## Abstract

**Introduction:**

There is uncertainty surrounding the diagnosis, prevalence, phenotype, duration and treatment of Long COVID. This study aims to (A) describe the clinical phenotype of post-COVID symptomatology in children and young people (CYP) with laboratory-confirmed SARS-CoV-2 infection compared with test-negative controls, (B) produce an operational definition of Long COVID in CYP, and (C) establish its prevalence in CYP.

**Methods and analysis:**

A cohort study of SARS-CoV-2-positive CYP aged 11–17 years compared with age, sex and geographically matched SARS-CoV-2 test-negative CYP. CYP aged 11–17 testing positive and negative for SARS-CoV-2 infection will be identified and contacted 3, 6, 12 and 24 months after the test date. Consenting CYP will complete an online questionnaire. We initially planned to recruit 3000 test positives and 3000 test negatives but have since extended our target. Data visualisation techniques will be used to examine trajectories over time for symptoms and variables measured repeatedly, separately by original test status. Summary measures of fatigue and mental health dimensions will be generated using dimension reduction methods such as latent variables/latent class/principal component analysis methods. Cross-tabulation of collected and derived variables against test status and discriminant analysis will help operationalise preliminary definitions of Long COVID.

**Ethics and dissemination:**

Research Ethics Committee approval granted. Data will be stored in secure Public Health England servers or University College London’s Data Safe Haven. Risks of harm will be minimised by providing information on where to seek support. Results will be published on a preprint server followed by journal publication, with reuse of articles under a CC BY licence. Data will be published with protection against identification when there are small frequencies involved.

**Trial registration number:**

ISRCTN34804192; Pre-results.

Strengths and limitations of this studyThis study does not start with an arbitrary definition of a new condition—‘opinion-based medicine’.Rather it represents ‘evidence-based medicine’—we will seek the views of children and young people on what they have experienced physically and mentally in the months following COVID-19.The study incorporates a comparator matched cohort of children and young people who have experienced a pandemic, school closure and social isolation but who had a negative COVID-19 test.The comparator matched cohort of children and young people must also have had a reason to seek a COVID-19 test: symptoms, anxiety, a contact or a bereavement.Ideally, we would test all children for antibodies to confirm COVID-19 positive and negative status throughout the study period but we thought this would significantly reduce participation.

## Introduction

Currently, there is huge uncertainty surrounding the diagnosis, prevalence, phenotype, duration and treatment of Long COVID. There is currently no diagnostic test or code for Long COVID. Consequently, cases of Long COVID are not captured in routine National Health Service (NHS) administrative data sets. Instead, Long COVID may be coded as a variety of different conditions in hospital or symptom clusters in non-hospitalised children and young people (CYP). However, it is possible the symptoms associated with Long COVID are in fact a mixture of factors relating to the pandemic and lockdown as a whole rather than the viral infection itself. For example, factors such as social isolation, anxiety, depression or educational concerns may be the root cause of these symptoms in CYP both with and without SARS-CoV-2 infection. The effects on the developing brain and behaviour of adolescents could be far reaching.^1^

Despite acute COVID-19 illness being milder in CYP, it should not be assumed that those CYP at low risk of life-threatening acute infections^2 3^ do not suffer the longer term consequences of SARS-CoV-2 infection. It is important to study Long COVID within this population given that the psychological and social impact of Long COVID could have major consequences for transition to adulthood. There is a clear need to define the clinical phenotype of Long COVID in order to understand those most at risk, the illness trajectory, and to provide accurate information on the natural course of the condition. It is equally important to understand both the physical and mental health impact on CYP with Long COVID, given the rise in mental health problems among CYP since the start of the pandemic.^4^ Obtaining a better understanding of which CYP are affected will help with targeting potential interventions.

The greatest risk factor for SAR-CoV-2 illness has been old age, with other risk factors at all ages including obesity, comorbid long-term conditions, learning and neurological disabilities, mental health problems and ethnic minority status. It is plausible that such CYP may be most at risk of suffering from Long COVID, given that much is still unknown in CYP about the immunological susceptibility and underlying biology of Long COVID. Of all CYP, those likely to be most at risk of Long COVID are teenagers, with existing literature showing they make up the majority of CYP with chronic fatigue, post viral syndromes and persistent symptoms.^5^

In adults, there is emerging evidence that gender is a risk factor for Long COVID, with middle-aged females more susceptible than men.^6^ In terms of symptoms, two main groupings have been identified: (1) respiratory symptoms (eg, cough, shortness of breath) as well as fatigue and headaches, and (2) multisystem, including the brain, gut and heart. Among adults with Long COVID, heart symptoms such as palpitations or fast heartbeat, pins and needles or numbness and problems concentrating (‘brain fog’) have been reported. Experiencing a greater number of symptoms during the first week of infection, as well as older age, has also been linked to Long COVID. It should be noted mental health conditions were not reported in this cohort. Four syndromes have been described in adults: postviral fatigue; fluctuating multisystem symptoms; postintensive care syndrome; and lasting organ damage. It is known in both adults and young people that a wide range of long-term physical conditions increase the risk of mental ill health, particularly if the condition involves the central nervous system, with several studies reporting increased rates of all common mental health conditions in children.^7^ Moreover, fatigue has also been studied in paediatric long-term conditions including CYP with multiple sclerosis.^8 9^ Emerging clinical observations and preliminary research indicate that COVID-19 can have a long-term impact on CYP in a range of domains^10 11^ but well-conducted, methodologically robust studies are lacking.

This study primarily aims to (A) describe the clinical phenotype and prevalence of post-COVID-19 symptoms (eg, pain or physical symptoms, fatigue, sleep problems, mental health problems) among test-positive CYP compared to test-negative CYP, (B) produce an operational definition of Long COVID in CYP, and (C) establish the prevalence of Long COVID in CYP testing positive for SARS-CoV-2 infection. The second aim is of particular importance given that this is a prerequisite for any future epidemiological or interventional study. This will be achieved by using the empirical data we will acquire from 17 000 CYP and a national Delphi consensus process.

## Methods

### Study design and setting

Public Health England (PHE) has been conducting national surveillance of SARS-CoV-2 since the start of the pandemic in England. PHE receives daily electronic notifications of all SARS-CoV-2 RT-PCR tests performed in healthcare settings (Pillar 1 tests) and in the community (Pillar 2 tests), which are reported through the Second Generation Surveillance System (SGSS). Information within the SGSS reports includes NHS number, name, age, sex, postcode, date of sample, reporting laboratory and test result. PHE also has access to the electronic Patient Demographic Service (PDS), which contains the names, addresses and status (alive/dead) of all patients registered with the NHS.

A sample of CYP aged 11–17 years when testing positive for SARS-CoV-2 between September 2020 and March 2021 and COVID-19 test-negative CYP matched for age, sex and region identified through SGSS will be linked to PDS using available identifiers and postal addresses. A letter will be posted to them, informing them about the study and inviting them to take part using an online link. This link will provide them with information about the study, with an option to consent online and complete a short recruitment questionnaire (or both as paper options). Recruitment was planned to start in March 2021 and all data collection anticipated to end in April 2023.

This will be a cohort study of SARS-CoV-2 test-positive CYP aged 11–17 years matched on the test date, age, sex and geography to SARS-CoV-2 test-negative controls identified by PHE.

### Participants

Between September 2020 and March 2021, a total of 234 803 CYP aged between 11 and 17 years were diagnosed with COVID-19 in England. During the same period there were 1 481 154 negative tests among this age group equivalent to 1 203 996 CYP. Among those who tested negative 76 689 individuals (100 154 tests) were excluded as they had a positive result before and/or after their negative test. The positive and negative cohorts were linked using age at test, gender, month of test and lower super output area resulting in 102 402 positive individuals and 147 561 negative individuals. Matched individuals were checked against the NHS spine to exclude any individuals who have died, and to extract participants’ addresses to send invitation letters. Thirty-seven individuals were excluded because they had died since their COVID-19 test (six among those positive and 31 among those negative), and 11 193 individuals of the positive cohort and 19 251 individuals of the negative cohort were excluded as an address was not available. Finally, 187 CYP were excluded as they were included in a previous study. Following exclusions, 91 016 positive CYP and 128 220 negative CYP will be available to be invited to participate in the study. For all the months except December, all eligible individuals will be sent an invitation. For those tested in December, 2970 positive CYP and 5911 negative CYP will be invited as the eligible number was so large that additional funding would be needed to invite all those eligible.

This is shown schematically in figure 1.

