### Statistical analyses

Response rates for positive and negative CYP will inform expectations of final study size and possibly refinement of the sampling percentages. Descriptive statistics will be used for all dimensions collected at baseline and the follow-up questionnaires, separately by test status, wave and month of test. Appropriate data visualisation techniques will be used to examine trajectories over time for those variables that are measured repeatedly, separately by test status and month of test. Summary measures of the fatigue and mental health dimensions will be generated using dimension reduction methods such as latent variables/latent class/principal component analysis methods. Cross-tabulation of latent variables against test status as well as discriminant analysis will help operationalise preliminary definitions of Long COVID. These will be compared with definitions based on categorisation of prolonged symptoms supplemented by a Delphi consensus process.

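### An excess of deaths among matched test-negatives signals that the comparator may contain more seriously ill young people, and the stated comparisons take no account of test setting or prior health

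*Protocol article*

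**What the plan says.** All references are to the protocol article.

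- **Source of tests** (Study design and setting). The surveillance feed covers tests "performed in healthcare settings (Pillar 1 tests) and in the community (Pillar 2 tests"). The listed fields are: "Information within the SGSS reports includes NHS number, name, age, sex, postcode, date of sample, reporting laboratory and test result". Reporting laboratory is among them; Pillar and prior illness are not.
- **Matching** (Participants). The cohorts were "linked using age at test, gender, month of test and lower super output area". The matched pools number 102 402 positives and 147 561 negatives.
- **Deaths** (Participants). "Thirty-seven individuals were excluded because they had died since their COVID-19 test (six among those positive and 31 among those negative"). Neither cause nor place of test is given, and the article does not comment on the imbalance.
- **Analysis** (Statistical analyses). Descriptive statistics are to be given "separately by test status, wave and month of test". The route to a definition is: "Cross-tabulation of latent variables against test status as well as discriminant analysis will help operationalise preliminary definitions of Long COVID". The resulting definitions are then compared with ones based on prolonged symptoms and a Delphi process.
- **Acknowledged limitation** (Strengths and limitations). Controls also had some reason to be tested. Testing in the course of care for another illness is not among the reasons listed, and the effect on the comparison is not discussed.

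**The concern.** A negative test taken in a healthcare setting can belong to a young person under care for something else. Matching on age, sex, month and small area does not balance this between the groups. The death counts are the only direct evidence in the article on the underlying health of the two groups, and they are unequal in the direction this mechanism predicts. Infection itself would, if anything, add deaths to the positive group.

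The Introduction links chronic physical illness to poorer mental health and notes that fatigue has been studied in such children. Fatigue and mental health are measured outcomes here. Extra illness among controls would raise their background symptom prevalence and shrink the positive-minus-negative difference (aim A). It would also make symptoms shared with ill controls look less discriminating when a definition is derived (aim B). A larger sample would not remove this bias.

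**Working it through.** **Inputs.** Deaths 6 and 31; matched pools 102 402 and 147 561; 76 689 of 1 203 996 negatives removed for a positive test at another time (all from Participants). Control prevalence 34%, difference 4 points, 2500 per group (Sample size).

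**1. Stated total.** 6 + 31 = 37, as printed.

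**2. Death risks.**
- Positives: 6 / 102 402 = 5.9 per 100 000.
- Negatives: 31 / 147 561 = 21.0 per 100 000.
- Risk ratio: 21.01 / 5.86 = 3.59.
- SE of log ratio: √(1/6 − 1/102 402 + 1/31 − 1/147 561) = 0.446; 95% CI exp(1.277 ± 1.96 × 0.446) = 1.50 to 8.59.
- Fisher exact p = 0.002; exact conditional interval 1.47 to 10.5.

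**3. Simple explanations.**
- Group size: at the positives' risk, 147 561 × 6 / 102 402 = 8.6 deaths would be expected among negatives, so about 22 are in excess.
- Removal of negatives who also tested positive: 76 689 / 1 203 996 = 6.4%. Even if none of those removed had died, the risk in the remainder rises at most 1 / (1 − 0.064) = 1.07-fold.
- Follow-up: person-time is not given. Month of test was matched, so a 3.6-fold gap in average follow-up is implausible, although some difference is possible with unequal group sizes.

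**4. Possible effect on symptom prevalence (assumptions, not document figures).** Excess death risk is 21.0 − 5.9 = 15.1 per 100 000. Suppose all of it comes from an extra, seriously ill subgroup of controls with mortality m. Its share is 0.0001515 / m, and control prevalence rises by share × (symptom prevalence in the subgroup − 34%).

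| Assumed mortality m | Share of controls | Rise if 70% symptomatic | Rise if 100% symptomatic |
|---|---|---|---|
| 5% | 0.3% | 0.11 points | 0.2 points |
| 1% | 1.5% | 0.55 points | 1.0 points |
| 0.5% | 3.0% | 1.1 points | 2.0 points |
| 0.1% | 15% | 5.5 points | 10 points |

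**5. Against the planned 4-point difference.** For 34% v 38% with 2500 per group, two-sided 5%, power is 83.8%, so the stated 80% is slightly conservative. If control prevalence rises by 0.5, 1 or 2 points while positives stay at 38%, power falls to 73%, 60% or 31%. The last row of the table exceeds 4 points and would take the observed difference past zero.

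**The case against.** The strongest objection is that 37 deaths in about 250 000 people, with no cause or test setting, say little about the questionnaire comparison. Those who died were excluded. The counts describe the matched pool, not the invited sample (December was subsampled) or the responders, and very ill young people may not complete a 20-minute questionnaire. The article is a condensed account, and covariate sets are commonly left to a fuller protocol or an SAP that is not shown.

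Much of this stands, and it rules out several stronger readings:

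- **That the test-negative group as a whole is sicker.** A risk of 0.02% is compatible with a very small, severely ill subgroup.
- **That bias towards zero has been shown.** The direction is plausible, but selective response could offset or reverse it.
- **That nothing, not even the matching variables, is accounted for.** Month of test is a matching variable and a stated stratifier. Discriminant analysis is multivariable, and the definition also draws on prolonged symptoms and Delphi consensus. The article states no adjustment for setting or prior health; it does not rule one out.
- **That a third or two-thirds of the planned difference is lost.** If 5% or 10% of controls were healthcare-tested with 60% prevalence, the rise would be 0.05 × 26 = 1.3 or 0.10 × 26 = 2.6 points, that is 33% or 65% of 4 points. Those shares and that prevalence are not in the documents and do not follow from the death counts.

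The objection does not remove the point. The article names its stratifiers and its route to a definition, and setting and prior health are in neither. The Sample size section mentions clinical data only for identifying risk factors for Long COVID. Followed as written, the plan would neither detect nor remove such an imbalance.

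**Conclusion.** The point holds as a warning signal. The excess of deaths among matched negatives is beyond chance and is not explained by group size or by the removal of negatives who also tested positive. The article gives a plausible mechanism, since both healthcare and community tests feed the sample, and states nothing that would address it.

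The effect on symptom differences cannot be determined from the documents. The range of about 0.1 to 5.5 points rests on three assumptions: that the excess deaths all come from one extra ill subgroup, that 70% of it is symptomatic, and that its mortality lies between 5% and 0.1%. It also assumes that this subgroup answers the questionnaire like everyone else. The low end is negligible against 4 points; the middle of the table is not.

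**What to change.** 1. Tabulate test setting by test status, using Pillar or, if it identifies setting, reporting laboratory. Do the same for any prior-health information collected, in both the invited sample and the responders.
2. Add a positive-negative contrast stratified by Pillar, or restricted to Pillar 2, as a sensitivity analysis.
3. Supplement the cross-tabulation with a regression of each outcome on test status, adjusted for the matching variables (age, sex, month, area), test setting, and prior health where held. Check whether the symptoms that separate the groups in the discriminant analysis change under the Pillar 2 restriction.

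**Cost.** Little analysis time, and probably a slight loss of sample in the restricted contrast. The main uncertainty is data: neither Pillar nor prior illness is among the listed surveillance fields, nothing says that reporting laboratory identifies Pillar, and the Outcomes section does not name pre-existing conditions. Availability must be confirmed first. If neither setting nor prior health can be obtained, the death imbalance should be reported as a limitation, with its plausible direction.

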**Figure 1 F1:**
[figure not shown]
Flow chart of the selection process. CYP, children and young people.

### Data collection

Participating families of CYP will be contacted 3, 6, 12 and 24 months after the CYP’s SARS-CoV-2 test (depending on recruitment month) and invited to take part in the study. Following online informed consent, the CYP will self-complete an online (or paper) questionnaire about their mental and physical health. CYP towards the lower end of the 11–17 age band and CYP with special educational needs or disability may require the help of a carer to complete the questionnaire.

### Outcomes

The questionnaires given to CYP include elements of the International Severe Acute Respiratory and emerging Infection Consortium (ISARIC) Paediatric COVID-19 follow-up questionnaire^12^ and the recent Mental Health of Children and Young People in England surveys^13^ to facilitate international comparisons regarding the risk factors and profile of Long COVID in CYP. The questionnaires given to CYP were designed together with the ISARIC Paediatric Working Group to produce a harmonised data collection tool, allowing for standardisation and meta-analysis by design.

The elements taken from the ISARIC Paediatric COVID-19 follow-up questionnaire^12^ include questions about demographics and physical symptoms, with particular questions enquiring about cough and fever, given that these are the main acute symptoms in non-hospitalised CYP^14^ and gastrointestinal symptoms, as a study has shown such symptoms were common in seropositive CYP.^15^ It is likely other symptoms will manifest later in Long COVID (eg, tiredness, headaches, myalgia, etc), with the skin rashes and cardiac problems in hospitalised children with paediatric multisystem inflammatory syndrome being borne in mind for Long COVID.^5^ Those older CYP could very well overlap with adult symptomatology (eg, a neuropsychiatric-encephalitic subgroup).

In terms of the other questions, the Strengths and Difficulties Questionnaire^16^ will be used to assess emotional and mental health, consisting of 25 items. The EuroQol Group, 5-Dimension health-related quality of life instrument for Young people (EQ-5D-Y)^17^ will be used as a measure of quality of life/functioning, with fatigue measured using the 11-item Chalder Fatigue Questionnaire.^18^ Additionally, the short 7-item version of the Warwick-Edinburgh Mental Well-being Scale^19^ will be included. Loneliness will be measured using the 4-item UCLA (University of California at Los Angeles) Loneliness Scale for Children^20^ as well as self-reported school attendance.

The length of the online self-assessment has an estimated completion time of approximately 20 min for CYP. The CYP do not have to complete all of the questions at once but can pause and save the answers at any point.

### Statistical analyses

Response rates for positive and negative CYP will inform expectations of final study size and possibly refinement of the sampling percentages. Descriptive statistics will be used for all dimensions collected at baseline and the follow-up questionnaires, separately by test status, wave and month of test. Appropriate data visualisation techniques will be used to examine trajectories over time for those variables that are measured repeatedly, separately by test status and month of test. Summary measures of the fatigue and mental health dimensions will be generated using dimension reduction methods such as latent variables/latent class/principal component analysis methods. Cross-tabulation of latent variables against test status as well as discriminant analysis will help operationalise preliminary definitions of Long COVID. These will be compared with definitions based on categorisation of prolonged symptoms supplemented by a Delphi consensus process.

